## Introduction

1

Lung cancer is the main cause of cancer in the world; approximately 1.6 million patients are diagnosed with lung cancer every year.^[1,2]^ It is the most familiar cause of deaths associated with cancer, with 1.3 million people dying from the disease each year, accounting for 1/5 of cancer deaths. Most lung cancers can be divided into small-cell lung cancer or non-small cell lung cancer. At the time of diagnosis, most patients have metastatic cancer or locally advanced cancer that is incurable, with a 5-year mortality rate of 85% to 90%.^[3]^ The treatment method for lung cancer is determined by the type of lung cancer, the disease stage, and the performance status of patients.^[4]^ The treatment methods involve radiation therapy, chemotherapy, surgical resection, palliative care as well as targeted therapy.^[5,6]^

The goal of treatment is to improve the life quality and prolong the life of patients with advanced lung cancer, or both. Nevertheless, due to poor functional status, many patients have limited treatment options. Many factors may lead to low functional status, involving comorbidities, high tumor burden, and older age.^[7]^ For the cancer progression, its direct effects include weight loss, shortness of breath, pain, and fatigue, together with some indirect influences of the cancer treatment, can accumulate to further deterioration in the life quality, sustained loss of physical health, and a decline in levels of physical activity.^[8,9]^ In patients with advanced lung cancer, the palliative care may have the greatest benefit, which may be due to the low life quality and heavy burden of symptoms of advanced lung cancer patients.^[10]^

The intervention of enhancing quality of life in patients (EQUIP) is a kind of supportive nursing intervention for the advanced lung cancer patients, which is dominated by nurses. It consisted of four educational sessions, led by a research nurse, on how to deal with the prevalent lung cancer symptoms, that is, worry, breathlessness, and fatigue. The objective of this present research is to evaluate the effect of the intervention of EQUIP in the advanced lung cancer patients.

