### Data collection

2.4

With the functional assessment of cancer therapy–lung, the measurement of life quality can be conducted.^[11]^ The 36-item tool measures emotional, physical, social, emotional, functional health and the symptoms specific to lung cancer. With Hospital Anxiety and Depression Scale, the measurement of mood is carried out.^[12]^ This 14-item tool consists of 2 subscales for depression and anxiety. This is a kind of categorical scale, and cut-off scores for each subscale are as follows: 0 to 7 represents normal, 8 to 10 represents mild, 11 to 14 represents moderate, and 15 to 21 represents severe.

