### Statistical analysis

2.5

All the data can be recorded into the software of Microsoft Excel 2013, and the analysis of all the data is carried out through utilizing the software of IBM SPSS Statistics for Windows, version 20 (IBM Corp., Armonk, NY). All the data are represented via the proper characteristics, for instance, median, mean, and percentage. The categorical variables and continuous variables are respectively analyzed using independent *t*-tests and χ^2^-tests. *P* value less than .05 indicates that there is statistical significance.

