## Results

3

Table 1 indicates the patient's life quality and Hospital Anxiety and Depression Scale in both groups.

**Table 1 T1:** Patient's life quality and HADS in both groups.

Outcomes	Study group (n = 45)	Control group (n = 45)	*P* value
Physical well-being			
Social well-being			
Emotional well-being			
Functional well-being			
Overall quality of life			
Anxiety subscale			
Normal			
Mild			
Moderate			
Severe			
Depression subscale			
Normal			
Mild			
Moderate			
Severe			

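### No outcome is named as primary and one P<.05 rule covers at least seven comparisons, so nothing fixes which result must support the conclusion that EQUIP improves quality of life

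*Protocol article*

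**What the plan says.** The objective in the Introduction is general: "The objective of this present research is to evaluate the effect of the intervention of EQUIP in the advanced lung cancer patients". It singles out no measure.

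Section 2.4 (Data collection) describes two instruments. FACT-L is used for quality of life. For mood: "With Hospital Anxiety and Depression Scale, the measurement of mood is carried out". On its structure: "This 14-item tool consists of 2 subscales for depression and anxiety", and each subscale is cut into four severity classes.

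Section 2.5 (Statistical analysis) assigns t-tests and chi-square tests and then gives one threshold for everything: a P "value less than .05 indicates that there is statistical significance".

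Section 3 contains the empty results table, titled "Patient's life quality and HADS in both groups". Its P value column runs over physical, social, emotional and functional well-being, then "Overall quality of life", then the anxiety and depression subscales with four severity lines under each.

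The conclusion, in the Abstract and in section 5, is already drafted as a single cautious statement that EQUIP may improve quality of life. No outcome is called primary in the Abstract, the objective, the data collection section, the analysis section or the table.

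**The concern.** The trial is meant to answer one question, whether EQUIP improves quality of life, but the plan holds at least seven comparisons of equal rank, each read at .05. Five of them are measures of quality of life. If one is significant and the others are not, the plan does not say whether the conclusion is supported.

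Two things follow. The error rate attached to the overall conclusion is not the one that a .05 threshold suggests. And the authors can decide which row is the headline after seeing the results, so a reader could not tell a prespecified success from the best of several rows.

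**Working it through.** **Inputs from the document**
- Per-test level: .05 (section 2.5). Sidedness is not stated; two-sided is assumed.
- Outcomes under the P value column of Table 1: 5 for quality of life and 2 HADS subscales. If each HADS subscale gets one test over its four classes, there are 5 + 2 = 7 tests. If each severity line gets its own test, there are 5 + 8 = 13.
- 45 patients per group (section 2.1).

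**Assumptions, because the document gives no figure**
- Common correlation between outcomes: 0 to 0.7.
- Overall quality of life is the sum of the four well-being subscales.

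The plan states no family-wise error rate and no power calculation, so there is no figure of its own to reproduce. The .05 threshold is an input.

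**Step 1: upper reference, independent tests**
- Either direction: 1 - 0.95^7 = 30.2% for seven tests; 1 - 0.95^5 = 22.6% for five.
- In favour of EQUIP, where each two-sided test spends .025: 1 - 0.975^7 = 16.2% for seven; 1 - 0.975^5 = 11.9% for five.

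Full independence cannot hold here if the overall score is built from its subscales, so these values are ceilings.

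**Step 2: allow for the dependence**

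Six normal test statistics with common correlation stand for the four subscales and two HADS scales. A seventh, overall quality of life, is the standardised sum of the four subscales. There is no true effect, the cut-off is 1.96, and each line uses 2,000,000 draws. All outcomes are oriented so that positive favours EQUIP.

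| Correlation | 7 tests, either direction | 7 tests, favouring EQUIP | 5 quality-of-life rows, either direction | 5 quality-of-life rows, favouring EQUIP |
|---|---|---|---|---|
| 0 | 28.2% | 15.0% | 20.4% | 10.6% |
| 0.3 | 24.6% | 12.4% | 18.0% | 9.0% |
| 0.5 | 20.8% | 10.4% | 15.8% | 7.9% |
| 0.7 | 16.5% | 8.2% | 13.1% | 6.6% |

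The comparators are 5% for either direction and 2.5% for a difference favouring EQUIP.

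**Step 3: does the normal approximation for HADS matter?**

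A patient-level simulation used 45 per group, five t-tests and two chi-square tests on four-class HADS data with assumed class proportions, over 6,000 runs. Its overall score was the sum of five subscales, including a lung-symptom subscale. The chance of at least one significant result among the seven tests was 28%, 25%, 23% and 19% at correlation 0, 0.3, 0.5 and 0.7. The range is similar to Step 2.

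**Step 4: after the fix**

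One named primary outcome tested two-sided at .05 carries an error of 5%, or 2.5% in favour of EQUIP.

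**The case against.** **The family is too wide for the stated conclusion.** HADS is described as measuring mood, and the conclusion speaks only of quality of life. This stands. The family that bears most directly on the conclusion is the five quality-of-life rows, at 13-20% in either direction or 7-11% in favour of EQUIP. That is still well above nominal.

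**No rule says that one significant row is enough.** A reader might infer from section 2.5 that any single P value below .05 establishes benefit. The text does not say so: it defines significance for a test and stops. The conclusion is hedged, and the Discussion speaks of acceptability and feasibility and asks for a further high-quality trial. This also stands. The defect is the absence of a rule linking results to the conclusion, not the presence of a bad one.

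**Multiplicity may be handled elsewhere.** The article is condensed and a separate analysis plan may exist. An adjustment procedure for secondary outcomes can fairly be left to that plan, and its absence is not criticised here. Naming the primary outcome is different. It belongs in the protocol, and here the article prints both the threshold and the table to which it will be applied.

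**The size depends on assumptions.** True: the number of tests and the correlations are assumed, which is why a range is given.

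**Conclusion.** The point holds. No outcome is primary, at least seven comparisons are read at .05, and nothing says which of them must support the conclusion on quality of life.

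Under seven two-sided tests, correlation from 0.7 to 0 and an overall score summed from four subscales, the chance of at least one false-positive difference is about 16-28% in either direction against 5%, and about 8-15% in favour of EQUIP against 2.5%. For the five quality-of-life rows alone it is about 13-20% and 7-11%.

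Three stronger readings are not supported:
- That the chance of a false claim of benefit reaches 30%. That figure needs seven independent tests and counts differences favouring control. In favour of EQUIP, seven tests cannot exceed about 16% even if independent.
- That every printed line of Table 1 is certain to be tested. Thirteen tests would give 1 - 0.95^13 = 48.7% if independent, but the layout does not settle whether the severity lines receive separate P values.
- That the plan promises a 5% error rate over all outcomes and breaks the promise. It makes no such statement.

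The lack of a primary outcome rests on none of the numerical assumptions; only its size does. It should be corrected before outcome data are examined.

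**What to change.** In the objective and in section 2.5, name overall quality of life, defined as the FACT-L total score at one fixed assessment time, as the single primary outcome. Test it two-sided at .05 and state that the conclusion depends on it alone. Say how the total is formed: section 2.4 says that the tool also covers lung-cancer symptoms, but Table 1 has no line for them.

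Label the well-being subscales and both HADS subscales as secondary, and report them as between-group estimates with 95% confidence intervals and no confirmatory claim. Any formal adjustment for them can be left to the analysis plan. In Table 1, mark the primary row accordingly.

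The cost is wording in the protocol and the table. It needs no extra patients, visits or instruments. The one small downside is that an isolated significant subscale can no longer carry the conclusion.

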## Results

3

Table 1 indicates the patient's life quality and Hospital Anxiety and Depression Scale in both groups.

**Table 1 T1:** Patient's life quality and HADS in both groups.

Outcomes	Study group (n = 45)	Control group (n = 45)	*P* value
Physical well-being			
Social well-being			
Emotional well-being			
Functional well-being			
Overall quality of life			
Anxiety subscale			
Normal			
Mild			
Moderate			
Severe			
Depression subscale			
Normal			
Mild			
Moderate			
Severe			

## Discussion

4

Lung cancer is one of the prevalent malignant tumors in the world.^[13,14]^ Like all cancers, the best hope for a cure for lung cancer is to early detect. Nevertheless, many lung cancer patients are diagnosed as advanced and often cannot be cured.

Palliative care is a concept in health care that has been developed over the past decade to solve the needs of supportive care associated with life-threatening diseases.^[15]^ Early palliative care can improve the symptom burden, patients’ quality of life, and enhance the survival rate.^[16]^ With the extensive evidence supporting the effect of palliative care in the improvement of patient outcomes, a new challenge is to optimize the resources to conduct effective services. EQUIP intervention is jointly developed via the interdisciplinary team of healthcare professionals, and these healthcare professionals have the relevant clinical expertise in locally managing lung cancer patients, involving professional palliative care nurses and care physicians, physiotherapists, and clinical psychologists. This is the first research to confirm the acceptability and feasibility of EQUIP intervention in advanced lung cancer patients. Further high-quality trial is still required to confirm our results.

## Conclusion

5

EQUIP intervention may be beneficial to improve the life quality in advanced lung cancer patients.
